### 2.10. Primary Outcome Measures

Pain intensity

The Visual Analog Scale (VAS) will be used to assess average pain intensity graded from 0 (no pain) to 10 (unbearable pain). Mild pain or no pain will be defined as VAS 0–3, moderate pain as VAS 4–6, and severe pain as VAS 7–10 [26]. Participants will be asked to rate their maximum pain intensity from the last 3 months.

2.Functional disability

The Revised Oswestry Low Back Pain Disability Index (ODI) will be used to assess the level of functional disability resulting from LBP. The questionnaire consists of 10 items related to different aspects of function regarding activities of daily living. Each item will be scored from 0 to 5, with higher values representing greater disability. The total score will be multiplied by 2 and expressed as a percentage [27].

3.Perceived musculoskeletal discomfort during prolonged sitting

The Borg CR-10 scale will be used to assess perceived musculoskeletal discomfort during 1 h of sitting, classified as prolonged sitting. The Borg CR-10 scale is presented in such a way that test subjects can indicate in which parts of the body they feel discomfort (i.e., neck, shoulder, upper back, lower back, hip/thigh, and knee) and the degree of discomfort they feel (on a scale from 0 to 10, 0 being no discomfort and 10 being extremely uncomfortable) [28]. The scale and body chart will be determined according to a standardized Nordic questionnaire [29]. During university classes, the participants will be required to spend an hour sitting in a chair with a backrest. The initial sitting position will be characterized by hips and knees at 90 degrees of flexion and a neutral ankle position with feet in full contact with the floor. During the 1 h of sitting, the participants will be instructed to avoid talking and to maintain the assigned sitting posture as much as possible. They will be able to make small adjustments if they feel too much discomfort. The Borg CR-10 scale will be given to the participants to complete after the one-hour sitting session.

4.Global perceived improvement

The Global Perceived Effect (GPE) scale will be used to assess the global perceived improvement of the condition. The investigator will ask the participant to rate, on a numerical scale, how much their condition has improved or deteriorated since some predefined timepoint: 1 = completely recovered, 2 = much improved, 3 = slightly improved, 4 = not changed, 5 = slightly worsened, 6 = much worsened, and 7 = worse than ever. These ratings will be dichotomized into “improved” (GPE scores 1–2) and “not improved” (GPE scores 3–7) [30]. 

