### 2.7. Assessment

Participants who fulfill the eligibility criteria, agree to participate, and sign a written informed consent form will be included in the study subject to the assessment. A blinded assessor-physiotherapist with five years of clinical experience will check the qualifying criteria. A baseline assessment will be conducted before participants are randomly assigned to groups. An outcome assessment will be collected at the start of the study and immediately after the 8-week intervention.

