### 2.9. Outcome Measures

Primary outcome measures (average pain intensity, functional disability, perceived musculoskeletal discomfort during prolonged sitting) will be collected at baseline and immediately after the 8-week intervention, and the global perceived improvement will be assessed immediately after the 8-week intervention. The secondary outcome measure (flexibility of the hamstring) will be collected after the 8-week intervention. Table 2 shows the distribution of the different measures across the timepoints during the study.

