### 2.12. Timeline of the Study

We designed the timeline of the study using the SPIRIT framework (Table 1). At enrollment, the purpose of the study and research procedures will be explained to the participants. The pre-screening will address the specific inclusion and exclusion criteria for the study, basic demographic data, and the frequency of LBP. Participants who meet the inclusion criteria will be invited to attend a baseline assessment (Table 2). All the tests will be performed during morning hours in the laboratory. 

At the baseline assessment session, participants will be requested to complete the VAS, ODI, and Borg CR-10 scale. After completion of the baseline assessment, participants will be randomly assigned to one of two groups (experimental or control), and simultaneous implementation of the exercise program will commence. After 8 weeks, all assessment measures for all participants will be repeated in the same way as the baseline measurements (Table 2).

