## Figures and Tables

**Table 1 jcm-13-04161-t001:** Exercises for active hamstring stretching with hip flexion mobilization.

1st part	
[figure not shown]	Foam roller massage. Starting position: sit on the mat with a straight spine, place the massage tool below the thigh, and roll the thigh between the buttock and the knee.
2nd part	
[figure not shown] [figure not shown]	Learning the pattern of flexion in the hip joints. Starting position: kneeling supported. Activation of the core muscles, and awareness of setting the lumbar spine in a neutral position. Moving the hips towards the heels, keeping the spine in a neutral position. Notes: keep the lower spine stable and the pelvis in an anterior tilt.
[figure not shown] [figure not shown]	Active stretching of hamstrings with the development of the habit of correct hip flexion and knee extension. Starting position: sit with a straight back, knees slightly bent. Flex hips and straighten knees. Hold. Knee flexion. Increase hip flexion and knee extension. Notes: keep the lower spine stable and the pelvis in an anterior tilt. The degree of flexion in the hips is adapted to the participant’s abilities.
[figure not shown] [figure not shown]	Active stretching of hamstrings with torso stabilization and correct hip flexion and extension; lumbar technique. Starting position: standing, facing the wall, legs slightly bent at the knees Hip flexion, then knee extension. Hold. Knee flexion. Hip flexion increase, knee extension. Notes: keep the lower spine stable and the pelvis in an anterior tilt. The degree of flexion in the hips is adapted to the participant’s abilities.

**Table 2 jcm-13-04161-t002:** SPIRIT table of enrollment, intervention, and assessment.

	Enrollment	Before Intervention	Randomization	Intervention
Timepoint	1st Month	2nd Month	2nd Month	3rd and 4th Months (8 Weeks)
Enrollment				
Eligibility pre-screening	+			
Informed consent	+			
Allocation			+	
Interventions				
Experimental and control group				+
Assessments				
Pain intensity		+		+
Functional disability		+		+
Perceived musculoskeletal discomfort		+		+
Global perceived improvement				+
Flexibility of the hamstring				+

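### The primary pain outcome is labelled average pain but asks for maximum pain over the last 3 months, so the week-8 score still covers about 5 pre-treatment weeks and can mask much or most of an effect

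*Protocol article*

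**What the plan says.** Section 2.9 of the protocol article lists the outcome as an average: "Primary outcome measures (average pain intensity, functional disability, perceived musculoskeletal discomfort during prolonged sitting". The pain item in Section 2.10 opens the same way, saying that the VAS "will be used to assess average pain intensity graded from 0 (no pain) to 10 (unbearable pain". The instruction to participants in that same item is different: "Participants will be asked to rate their maximum pain intensity from the last 3 months".

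On timing, Section 2.7 states "An outcome assessment will be collected at the start of the study and immediately after the 8-week intervention", and Section 2.9 says that the primary measures "will be collected at baseline and immediately after the 8-week intervention". Section 2.12 adds "After 8 weeks, all assessment measures for all participants will be repeated in the same way as the baseline measurements". Table 2 places the intervention in the "3rd and 4th Months (8 Weeks" column. No shorter recall period is given for the follow-up visit.

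**The concern.** There are two faults in one item.

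- **Label against question.** An average and a maximum are different quantities. A result reported under the label in Section 2.9 would describe something participants were not asked. An analysis plan cannot repair this, because the fault lies in the wording put to participants.
- **Recall window against follow-up time.** A 3-month look-back taken at 8 weeks reaches past the start of treatment. Under Section 2.2 participants must have had pain for at least 3 months at entry, so the pre-treatment part of the window belongs to an established pain history. Asking for a maximum makes the overlap worse, because one bad week before treatment can set the follow-up score.

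Pain is the first-listed primary outcome, and the Introduction gives reduction of low back pain as an aim. If the item can hardly move, a null pain result could not be told apart from an insensitive question.

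**Working it through.** The plan gives no expected pain difference, SD or recall calculation, so there is no figure of its own to reproduce on this point.

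**Step 1: the overlap.** Inputs: recall of 3 months (Section 2.10); follow-up immediately after 8 weeks (Sections 2.7 and 2.9); same procedure at both visits (Section 2.12).

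- 3 months ≈ 13 weeks: 13 − 8 = 5 pre-treatment weeks; 5/13 = 38%.
- 3 months read as 12 weeks: 12 − 8 = 4 pre-treatment weeks; 4/12 = 33%.

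Counting from the start of treatment, the baseline window runs from about week −13 to 0 and the follow-up window from about week −5 to +8. The two share weeks −5 to 0.

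**Step 2: direction of the bias.** Let A be the worst pain in the shared pre-treatment weeks, B the worst pain in the 8 later weeks without treatment, and δ an immediate reduction. With accurate recall the follow-up score is max(A, B) without treatment and max(A, B − δ) with it. The difference is 0 if A ≥ B, and the smaller of δ and B − A otherwise. It can never exceed δ, and it is below δ for everyone with B − A < δ. The group difference is therefore pulled toward zero. It also levels off as δ grows, so larger effects lose a larger share.

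If a participant's worst pain in the whole baseline window fell in weeks −5 to 0, the follow-up score cannot be lower than the baseline score.

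For a very small immediate effect and weeks that are alike, the share kept is the chance that the peak falls in a treated week: 8/13 = 62%.

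**Step 3: size, by simulation.** All inputs are assumptions: person mean of weekly peak pain 4.5 with SD 1.5; week-to-week SD 0.5 to 1.5; onset immediate or ramping over 4 to 8 weeks; perfect recall; 13-week window. Share kept = (group difference in the 13-week maximum) ÷ (group difference in the week-8 peak).

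| True reduction in weekly peak | Onset | Difference seen | Share kept |
|---|---|---|---|
| 2 points | immediate or ramp | 0.2–0.7 points | 11–35% |
| 1 point | immediate or ramp | 0.2–0.5 points | 18–47% |
| 0.5 points | immediate | not tabulated | 40%, 51%, 54% at weekly SD 0.5, 1.0, 1.5 |

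A re-run under these assumptions gave the same shares. A second model (mean 5, between-person SD 1, weekly SD 0.5 to 2, weekly autocorrelation 0 or 0.5) kept 8–48% for reductions of 1 to 3 points. It also shows the levelling-off: with weekly SD 0.5 and immediate onset, a 1-point and a 2-point reduction both appear as about 0.25 points. On a 12-week window with weekly SD 2, an immediate 1-point reduction keeps 53%.

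**Step 4: how much of the loss comes from the pre-treatment weeks.** A maximum over the 8 treatment weeks alone keeps essentially all of an immediate effect, about 56–79% under a 4-week ramp and about 36–54% under an 8-week ramp. With immediate onset, the pre-treatment weeks explain essentially the whole loss. With gradual onset, part of it comes from taking a maximum over a period in which the effect is still building.

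**The case against.** **The 3-month question may be meant as baseline history.** Section 2.8 does ask about pain in the last three months before randomisation. But the disputed sentence stands in the outcome definition in Section 2.10, and Section 2.12 says "all assessment measures for all participants will be repeated in the same way as the baseline measurements". If baseline only was intended, the text still needs correcting, and the two visits would then measure different things.

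**The size is not known.** This stands. The documents give no pain SD, weekly variation or onset pattern. A reader might infer that the item hides most of any effect. The figures do not support that: an immediate 0.5-point effect keeps more than half in two of the three cases above, and so does the 12-week case with weekly SD 2.

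**Recall is not perfect.** This also stands. Participants who weight recent pain would show less dilution, so the item cannot be called insensitive by construction. Still, a primary outcome should not depend on participants disregarding the stated recall period.

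**Some participants can still improve.** A reader might infer that anyone whose follow-up peak was before treatment cannot show a lower score. That holds only if the worst week of the whole baseline window fell in the last 5 weeks. Someone whose baseline peak came earlier can score lower.

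**Scope.** Disability, sitting discomfort and global perceived improvement are not stated to use this window. The bias is toward zero on one outcome and does not create a false benefit.

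**Conclusion.** Wrong as written. Three things follow from the text alone: the label and the question contradict each other; about 5 of 13 weeks recalled at follow-up (4 of 12 on the shorter reading) precede treatment; and with accurate recall the bias in the group difference is toward zero.

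The size does not follow from the text. Under the stated assumptions, a 1 to 2 point reduction keeps about 11–47% of its week-8 size and an immediate 0.5-point reduction about 40–54%. The supportable statement is that the item can mask much or most of an effect on pain, partly through the pre-treatment weeks and, with gradual onset, partly through the use of a maximum.

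**What to change.** Use one definition at both visits. Average pain matches the label already in Sections 2.9 and 2.10. Set a recall window that at week 8 lies wholly inside the treatment period, preferably near its end. Average low back pain over the last 7 days on the 0–10 VAS is one example; the documents do not dictate the exact length. Remove the 3-month maximum from the outcome definition and keep that question as screening history only.

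The cost is one questionnaire line, a protocol amendment and an update of the registered outcome. Section 2.1 says the trial is prospectively registered; the record is not available here, so its wording has to be checked. Participants who have already started treatment cannot supply an untreated baseline on the new item. They could still give the week-8 value, but would not contribute to the group-by-time analysis in Section 2.13.

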### 2.11. Secondary Outcome Measures

#### Flexibility of the Hamstrings

The flexibility of the hamstrings will be assessed using the single passive straight leg raise (SLR) test [31], measured in degrees by a goniometer. The SLR will be performed twice for each leg and the mean value of the two attempts will used for analysis [31]. A subject’s hamstring muscles will be considered tight (in a shortened position) if the SLR is ≤70° [32]. 

### 2.12. Timeline of the Study

We designed the timeline of the study using the SPIRIT framework (Table 1). At enrollment, the purpose of the study and research procedures will be explained to the participants. The pre-screening will address the specific inclusion and exclusion criteria for the study, basic demographic data, and the frequency of LBP. Participants who meet the inclusion criteria will be invited to attend a baseline assessment (Table 2). All the tests will be performed during morning hours in the laboratory. 

At the baseline assessment session, participants will be requested to complete the VAS, ODI, and Borg CR-10 scale. After completion of the baseline assessment, participants will be randomly assigned to one of two groups (experimental or control), and simultaneous implementation of the exercise program will commence. After 8 weeks, all assessment measures for all participants will be repeated in the same way as the baseline measurements (Table 2).

### 2.13. Data Analysis

The normality of the distributions will be checked using the Shapiro–Wilk test. Data will be presented as mean ± SD where appropriate. For variables that do not meet the criteria of normality of distribution, data will be presented as medians and quartile ranges. Lavene’s test will be conducted to verify the homogeneity of variances. The chi-square test will be used for categorical variables. The Mann–Whitney U test will be used to compare the groups. The mixed-design ANOVA with two factors (intervention, time) will be used. Tukey’s post hoc test will be used for detailed comparisons. Effect sizes will be assessed by partial eta squared (ANOVA) or the Glass rank-biserial correlation coefficient (the Mann–Whitney U test). The significance level will be set at *p* < 0.05.

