### 2.3. Sample Size

The necessary minimum total number of subjects (n = 44) was obtained using the G*power program assuming a medium-sized effect (d = 0.50) at a significance level of 0.05 and a statistical power of 0.85. The sample will be increased by 10% to compensate for possible dropouts (overall sample = 48 participants). 

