### 2.4. Randomization

Eligible participants will be randomly assigned to one of two groups: the experimental group (education, hamstring stretching, core stabilization, hip flexion mobilization) or the control group (education without any specific exercises). The randomization will be carried out by a researcher external to the study using a Microsoft Excel software random number generator before the beginning of the main study. Concealed allocation will be achieved using opaque envelopes. After the baseline assessment, the researcher responsible for the intervention will open the envelope to identify the group to which the participant will be allocated.

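### The planned mixed-ANOVA test is valid but less efficient than baseline-adjusted ANCOVA, and section 2.13 does not say which named test decides an outcome

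*Protocol article*

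**What the plan says.** Section 2.13 of the protocol article names three procedures for the group comparison:

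- "The mixed-design ANOVA with two factors (intervention, time) will be used".
- "The Mann–Whitney U test will be used to compare the groups". No outcome, time point or condition is attached.
- Tukey's "post hoc test will be used for detailed comparisons".

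A Shapiro–Wilk check comes first, but the section links its result only to how data are presented (mean and SD, or median and quartiles). Effect sizes are to be partial eta squared for the ANOVA or a rank-biserial coefficient for Mann–Whitney. Categorical variables go to a chi-square test. The section names no baseline-adjusted analysis.

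The design is simple. Section 2.4: "Eligible participants will be randomly assigned to one of two groups". Section 2.7: "An outcome assessment will be collected at the start of the study and immediately after the 8-week intervention". According to section 2.12, VAS, ODI and Borg CR-10 are all completed at baseline. Global perceived effect (GPE) is rated only after the intervention and is dichotomised (sections 2.9 and 2.10).

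**The concern.** With two arms and two time points, the interaction of a mixed ANOVA compares mean change between arms. Subtracting the whole baseline value adds noise unless baseline and follow-up are very highly correlated. ANCOVA subtracts only the part of baseline that predicts the outcome. The trial is small and already collects the baselines, so the lost precision could be recovered at almost no cost.

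The second issue is precedence. Two between-group tests are named and neither is said to decide. The section also does not say that the interaction, rather than a main effect, is the treatment effect. The time main effect is not a randomised comparison, and the group main effect averages in the baseline.

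Third, a 2 x 2 table has six pairwise Tukey comparisons. Two are before/after changes within one arm. Participants enter because they have pain, so scores may fall without any treatment effect.

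**Working it through.** **Inputs**

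- Total N = 44. Section 2.3: "The necessary minimum total number of subjects (n = 44) was obtained using the G*power program". I take 22 per arm; equal allocation is an assumption.
- Effect and error rates. Section 2.3: "assuming a medium-sized effect (d = 0.50) at a significance level of 0.05 and a statistical power of 0.85". Sidedness is not stated; I use two-sided.
- Two arms and two time points (sections 2.4 and 2.7), so the interaction has 1 degree of freedom.
- Correlation rho between baseline and week 8: not in the documents. Assumed range 0.3 to 0.9.
- Equal SD at both times, with d in units of that SD: assumption.

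**The plan's own figure.** I could not reproduce 44 for a two-group comparison. A two-sided two-sample t-test at d = 0.5 and 85% power needs 73 per arm (146 in total). A within-between repeated-measures ANOVA with f = 0.25 needs 46 at rho = 0.4 and 38 at rho = 0.5, so 44 would need an unstated rho near 0.4. That is a separate matter; this point uses 44 and d = 0.5 only as the planned setting.

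**Variance comparison** (SD = 1)

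- Change score: 2(1 − rho)
- ANCOVA: 1 − rho²
- Ratio, ANCOVA to change: (1 − rho²) / [2(1 − rho)] = (1 + rho)/2

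The ratio is below 1 for every rho below 1.

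**Power.** Noncentral t with noncentrality (0.5/√variance) × √(22 × 22/44), where the last factor is √11 = 3.317. Degrees of freedom are 42 for the change score and 41 for ANCOVA. At rho = 0.5 the change-score variance is 1.00, so the noncentrality is 0.5 × 3.317 = 1.66. The ANCOVA variance is 0.75, so it is 0.577 × 3.317 = 1.91.

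| rho | Variance ratio | Power, group-by-time | Power, ANCOVA | Total N for 85%: change / ANCOVA |
|---|---|---|---|---|
| 0.3 | 0.65 | 27.8% | 39.7% | 204 / 134 |
| 0.5 | 0.75 | 36.7% | 46.4% | 146 / 110 |
| 0.7 | 0.85 | 55.2% | 62.1% | 90 / 76 |
| 0.8 | 0.90 | 72.6% | 77.0% | 60 / 54 |
| 0.9 | 0.95 | 95.2% | 96.0% | 32 / 30 |

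Mann–Whitney on week-8 scores has about 35% power whatever rho is, because it ignores baseline.

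**Simulation check** (10,000 trials per setting, 22 per arm, d = 0.5, rho 0.3 / 0.5 / 0.7). Change-score test: 27.9 / 37.1 / 55.6%. ANCOVA: 39.3 / 45.8 / 61.1%. The simulated ANCOVA power is up to 1 point below the formula, so at rho = 0.9 the two methods should be treated as equal in practice.

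**Two tests on one outcome.** In the same simulations the change-score test and Mann–Whitney on week-8 scores disagreed on significance in 28%, 32% and 41% of trials. With no effect, at least one was significant in 9.0% to 9.4% of trials, against a nominal 5%. These figures apply only if both tests are run on one outcome; the error rate further requires that either may count.

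**The case against.** The strongest reply is that nothing here is an invalid test. Under randomisation the interaction is unbiased and holds its alpha, so ANCOVA is a recommendation on efficiency. That stands. A reader might infer that the mixed ANOVA is wrong for this design; the documents do not support that.

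A reader might also infer that the plan carries a 9% type I error. It does not say so. The normality check and the word joining the two effect sizes suggest that Mann–Whitney is a fallback. It could also serve hamstring flexibility, which section 2.9 and Table 2 schedule only after the intervention. Under a fallback chosen by Shapiro–Wilk (22 per arm, no effect, 6,000 runs per setting), simulated type I error was 5.0–5.2% for normal data and 4.4–5.3% for skewed data. The 9% is therefore a worst case. What remains is that the section attaches no such rule to the choice of test.

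Three further inferences fail:

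- GPE is not left without a method. It is dichotomised, and section 2.13 gives categorical variables a chi-square test.
- Participants without a week-8 value are no argument for ANCOVA, because a complete-case ANCOVA loses them too. An article may leave the handling of missing data to a fuller document.
- Nothing says that within-arm changes will be read as the treatment effect. The Tukey set includes them, but it also includes the between-arm comparison at week 8.

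Finally, the gain depends on an unknown rho. Section 2.10 asks for maximum pain over the last 3 months. At week 8 that window (about 13 weeks) still reaches about 13 − 8 = 5 weeks before baseline, which may raise rho for VAS and shrink the gain. This is inference, but it is a fair reason to show the range up to 0.9.

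**Conclusion.** The point holds as lost efficiency plus no stated precedence between tests. Switching to ANCOVA is worth about 12 power points at rho = 0.3, 10 at 0.5, 7 at 0.7, 4 at 0.8 and under 1 at 0.9. This assumes 22 per arm, d = 0.5, a two-sided 5% level and equal SDs. The direction does not depend on rho, apart from the one degree of freedom; the size does.

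One might hope that ANCOVA repairs the sample size. It does not: at N = 44 its power is 77% at rho = 0.8, still short of the 85% target, and reaches that target only at a higher rho. It also gives one answer per outcome, not one for the trial, because several primary outcomes remain and multiplicity across them is untouched.

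**What to change.** In section 2.13, for each outcome with a baseline value (VAS, ODI, and Borg CR-10 as the protocol defines it), make the deciding test the between-group difference at week 8 from ANCOVA with the baseline value as covariate, reported with a 95% CI.

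If residuals are clearly non-normal, use rank-ANCOVA or a bootstrap CI for that same baseline-adjusted comparison, in place of a separate unadjusted Mann–Whitney test. State that within-arm Tukey comparisons will not be used as evidence of effect. Leave GPE with the chi-square test.

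The cost is analysis wording and one degree of freedom. The baselines are already scheduled, so no new data or visits are needed, and the set of primary outcomes does not change. The wording should be fixed before outcome data are seen by arm.
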